### Patient Enrollment and Group Allocation

All patients with SMLC being treated at our center are potential candidates, and those who meet the inclusion and exclusion criteria will be eligible for enrollment in our study. Patients who receive surgical treatment along with postoperative systemic comprehensive treatment will be enrolled in the surgical group. Patients who receive only conservative treatment (eg, radiotherapy, chemotherapy, targeted molecular therapy, immunological therapy, etc) without surgical treatment will be enrolled in the nonsurgical group. All study procedures, as well as the participants’ rights, responsibilities, benefits, and risks, will be communicated, and participants will sign an informed consent form. Figure 1 displays the study flowchart.

In order to participate, patients will need to meet certain eligibility criteria. The inclusion criteria are (1) a pathological diagnosis of SMLC, (2) understanding and voluntarily participating in the study, and (3) being regularly followed up beyond 2 years or to the endpoint. Exclusion criteria include: (1) not receiving antitumor treatment at our hospital, (2) coexistence of spinal trauma or infection, (3) history of other malignancies, and (4) unwillingness to participate or inability to adhere to our follow-up schedule.

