### Treatment

A surgical decision is made following the advice of our institutional multidisciplinary treatment team for spinal metastasis. There are 3 indications for surgery at our center: severe yet drug-resistant local pain, progressive neurological dysfunction, and emerging or latent spinal instability. Otherwise, patients are referred for nonsurgical treatment.

In the surgical group, patients are given surgical treatment, neurological rehabilitation, and adjuvant therapies (ie, SBRT and antitumor drugs). In this setting, we have established a synchronized workflow for surgery-based multimodality therapy instead of the conventional step-by-step schedule. A synchronized workflow means that neurological rehabilitation is incorporated and commenced right before the surgery and that SBRT and antitumor drugs are started early and simultaneously during the process of rehabilitation.

In the nonsurgical treatment group, patients are treated with adjuvant therapies exclusively, including radiotherapy, chemotherapy, targeted therapy, immunological therapy, etc. Considering the existence of various adjuvant modalities, this study will only enroll patients who receive both locoregional radiotherapy and antitumor drugs.

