#### Secondary Outcomes

Secondary outcomes include the following:

The progress-free survival period, defined as the time after the start of antitumor therapies until disease progression.Recovery of SMLC-related symptoms, defined as the relief of locoregional pain, which is measured by visual analogue scale (VAS) values, and the recovery of neurological status, which is assessed using the American Spinal Injury Association (ASIA) score. Immediate improvement in VAS and ASIA scores is assessed before discharge.Recovery of self-care performance, assessed using the Karnofsky Performance Scale (KPS) score and the Eastern Cooperative Oncology Group (ECOG) performance score.Quality of daily life, assessed by the Short Form 36 Health Survey Questionnaire.

Other outcomes for evaluation include complications in antitumor treatment. Surgical complications are rated according to the system proposed by Clavien et al [22], whereas toxicity of radiotherapy and antitumor drugs is graded using the National Cancer Institute’s Common Toxicity Criteria for Adverse Events (version 5.0). The endpoint of the study is the death of the recruited patient. The primary outcome is assessed by the endpoint of the study, whereas secondary and other outcome metrics are assessed at each visit.

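### Read literally, the surgical-group definition leaves operated patients who never start systemic treatment out of the surgical complication rate

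*Protocol article*

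**What the plan says.** The protocol article defines both groups by treatment received. Under Patient Enrollment and Group Allocation: "Patients who receive surgical treatment along with postoperative systemic comprehensive treatment will be enrolled in the surgical group". Patients treated conservatively "without surgical treatment will be enrolled in the nonsurgical group". The same section requires "being regularly followed up beyond 2 years or to the endpoint", and Secondary Outcomes explains that "The endpoint of the study is the death of the recruited patient".

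On harm, Secondary Outcomes says: "Other outcomes for evaluation include complications in antitumor treatment". It continues: "Surgical complications are rated according to the system" of a named classification. No separate population for this outcome is given, and no expected rate.

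The Treatment section says the multidisciplinary team makes the surgical decision. It describes stereotactic radiotherapy and antitumor drugs as starting early, during rehabilitation, with no time window.

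**The concern.** Receiving postoperative systemic treatment is an event after surgery, and a serious surgical complication can prevent it. If membership of the surgical group depends on that event, the complications most likely to be missed are those severe enough to stop further treatment. The reported rate would describe operated patients who went on to systemic therapy, not the risk facing a patient who is offered surgery.

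This matters because the article expects its findings to support a surgical strategy (Expected Findings), and surgical complications are the harm to set against any benefit. Strengths and Limitations also presents the study as a test of the feasibility of synchronized adjuvant therapy after surgery. Operated patients who never start that therapy are the clearest failures of feasibility.

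The Background makes some early loss plausible. It reports median survival after surgery of 2 to 14 months across studies, and says the recommended timing of adjuvant radiotherapy is hard to keep in practice. Delay is not the same as never starting, so this shows only that the group may not be empty.

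**Working it through.** **Who fits where.** Take an operated patient who never starts postoperative systemic treatment.

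- Surgical group: the definition asks for surgery along with that treatment, so the patient does not meet it.
- Nonsurgical group: limited to patients without surgery, so the patient does not meet it.
- Follow-up criterion: met even after an early death, because follow-up to the endpoint is enough and the endpoint is death. This criterion is not what removes the patient.
- Complication outcome: no other denominator is named, so the patient is not counted.

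**The plan's own figures.** The article gives no complication rate and no never-start share. Its figure of 66 per group reproduces (two-sided, common variance (4² + 3²)/2 = 12.5): 2 × (1.960 + 1.282)² × 12.5 / 2² = 65.7, rounded up to 66. This point does not affect it. The relevant inputs are about 25 operations a year, 5 years of enrolment and a target of 120 (Sample Size and Study Timeline):

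- 25 × 5 = 125 operations
- (125 − 120)/125 = 5/125 = 4.0%

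If the target is met from about 125 operations, at most 4% can be left out for any reason, including refusal and the other exclusions.

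**Size of the bias.** Let r be the major-complication rate among all operated patients, f the share who never start, and p the rate among never-starters. All three are assumed.

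- Reported rate = (r − f·p)/(1 − f)
- Understatement = r − reported rate = f·(p − r)/(1 − f)

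Understatement in percentage points:

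| r | f | p = r | p = 50% | p = 80% | p = 100% |
|---|---|---|---|---|---|
| 20% | 1% | 0 | 0.30 | 0.61 | 0.81 |
| 20% | 4% | 0 | 1.25 | 2.50 | 3.33 |
| 10% | 1% | 0 | 0.40 | 0.71 | 0.91 |
| 10% | 4% | 0 | 1.67 | 2.92 | 3.75 |

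The extreme case in counts at r = 20%: 25 of 125 is the true rate, and (25 − 5)/(125 − 5) = 20/120 = 16.67% is reported.

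**Against sampling error at n = 120.**

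- r = 20%: 1.96 × √(0.2 × 0.8/120) = 7.16 points; 3.33/7.16 = 0.47
- r = 10%: 1.96 × √(0.1 × 0.9/120) = 5.37 points; 3.75/5.37 = 0.70

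The largest bias is about 0.5 to 0.7 of the 95% confidence interval half-width. Unlike sampling error, it does not shrink with more patients.

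**If accrual does not go as planned**, the 4% ceiling no longer applies. With a starters' rate s = 20% and p between 50% and 100%, the understatement f·(p − s) is 3 to 8 points at f = 10% and 4.5 to 12 points at f = 15%. Nothing in the article points to shares that high.

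**The case against.** The strongest reply is that the enrolment sentence summarises two treatment pathways and was not meant to screen on later events. The Treatment section describes adjuvant therapy as given to patients already in the surgical group, after a team decision to operate. The accrual plan counts patients undergoing surgery and deducts nobody for failing to start. The study flowchart is not shown, and a full protocol may settle the matter. This strategy reading is plausible. What remains is that the sentence governing entry is written in terms of what patients receive, and nothing shown restores those who never start. A stated rule that selects on a later event is more than an omitted detail.

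Three stronger readings are tempting, and the documents do not support them.

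- *Two further sentences remove the same patients.* One exclusion is "not receiving antitumor treatment at our hospital". It would apply only if surgery alone is not antitumor treatment, yet Secondary Outcomes lists surgical complications among complications of antitumor treatment. The Treatment section also says "this study will only enroll patients who receive both locoregional radiotherapy and antitumor drugs", but this stands in the paragraph on the nonsurgical group. Neither is a demonstrated second route of loss.
- *Overall survival is biased in favour of surgery.* The same selection could lengthen survival in the surgical group. With an assumed 5% never starting and surviving 1 to 3 months against 11 for starters, the mean would be overstated by 0.05 × (11 − 3) = 0.4 to 0.05 × (11 − 1) = 0.5 months, against a planned difference of 2. The nonsurgical group is also conditioned on treatment received, so the net effect is unclear.
- *The bias is large.* Every rate is assumed, and zero belongs in the range.

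It also stands that this is an other outcome, neither primary nor secondary.

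**Conclusion.** The point holds as a defect of wording with a limited consequence. Followed literally, the group definition leaves operated patients who never start systemic treatment out of the surgical complication rate. The direction is downward if they have more complications than starters.

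The size is unknown: zero if the rates are equal, and up to about 3 to 4 percentage points if the true rate is 10% to 20% and 120 patients are enrolled from about 125 operations. The upper end needs all five spare patients to be never-starters with major complications and no other loss, so it is a ceiling under that accrual and not an estimate. That the bias is probably small is a judgement resting on this narrow margin and on the planned early start of therapy. No sample size or specific test depends on the outcome.

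**What to change.** State under Secondary Outcomes that surgical complications are counted from the date of surgery among all consenting patients who undergo surgery for spinal metastases of lung cancer with postoperative therapy planned, whether or not it starts. Grade perioperative death highest. Report how many operated patients never started postoperative therapy, with reasons.

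Changing the complication denominator is enough for this point. If the surgical group itself is redefined in the same way for overall survival, classify the nonsurgical group by planned treatment too. Otherwise early deaths would be kept among operated patients but dropped from the nonsurgical group, which must receive both radiotherapy and drugs, and the comparison would be biased against surgery.

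The change is a short wording amendment at one center, with three costs. Consent has to be taken before surgery, and the article does not say when it is taken now. For patients operated on since June 2022 a look-back is needed, and those who died without consenting can at most be counted. The reported complication rate may also look slightly less favourable.

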## Methods

### Study Design

This study is a prospective cohort study. We will compare the treatment outcomes of surgical and nonsurgical methods for SMLC in a real-world clinical scenario. The study will enroll 240 patients (120 patients in the surgical group and 120 patients in the nonsurgical group) from June 1, 2022, to June 30, 2027. The patients will be visited postoperatively at 3, 6, 12, and 24 months. The study is due to be completed on June 30, 2029.

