### Sample Size and Study Timeline

In this study, we plan to compare the overall survival (OS) time between the two groups and explore its prognostic factors. The sample size calculation was based on the survival time and estimation of influencing factors. According to an unpublished retrospective study performed at our center and previous literature [20,21], the average OS time was 11 (SD 4) months in the surgical group and 9 (SD 3) months in the nonsurgical group. Assuming an overall Type 1 error (α) of .05 and Type II error (β) of .1, we need 66 patients in each group. Additionally, there are 12 predictive factors we plan to analyze in the prediction model. According to the sample size estimation method for multivariable regression models, 100 cases in each group are needed (the ratio of surgical to nonsurgical group is 1:1). Considering a final follow-up rate of 80%, a minimum of 120 patients will be required for each group. There were approximately 25 patients undergoing surgery per year at our center; therefore, we plan to enroll the patients over the next 5 years. Since more patients are treated nonsurgically than surgically, all nonsurgical patients treated during the first 5 years will be enrolled.

The study duration is estimated to be 7 years to ensure that all recruited patients are followed up for 2 years. Each visit’s timeline and tasks are presented in Multimedia Appendix 1.

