### Outcomes

#### Primary Outcome

The primary outcome metric of the study is the OS period. OS is defined as the time after the start of any antitumor therapy for SMLC to death of any cause.

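### Inclusion criterion (3) depends on future follow-up; if applied as written, it excludes patients lost alive before 2 years and makes eligibility depend on overall survival

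*Protocol article*

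**What the plan says.** Under Patient Enrollment and Group Allocation, the protocol article introduces its criteria with "In order to participate, patients will need to meet certain eligibility criteria". The third inclusion criterion is "being regularly followed up beyond 2 years or to the endpoint". The Secondary Outcomes section fixes what the endpoint is: "The endpoint of the study is the death of the recruited patient".

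Three other statements bear on this:

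- Study Design: "This study is a prospective cohort study".
- Primary Outcome: "OS is defined as the time after the start of any antitumor therapy for SMLC to death of any cause".
- Sample Size and Study Timeline: "Considering a final follow-up rate of 80%, a minimum of 120 patients will be required for each group".

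Willingness and ability to attend are handled separately, by exclusion criterion (4): "unwillingness to participate or inability to adhere to our follow-up schedule". The Statistical Analysis section plans Kaplan-Meier curves, the log-rank test and Cox regression. The article does not say that patients lost alive are kept and censored, and it does not say that they are dropped.

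**The concern.** An eligibility criterion for a prospective cohort has to be decidable when the patient enters. This one is decided up to 2 years later, and partly by the primary outcome. A patient satisfies it by dying under observation or by being followed alive past 2 years. A patient last seen alive at 10 months satisfies neither limb.

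Applied literally, the rule discards valid censored survival time and keeps every observed death. Kaplan-Meier and Cox methods cope with censoring, but they cannot recover patients whom the eligibility rule has removed. The OS estimate, the surgical versus nonsurgical comparison and the survival prediction model would all then rest on a cohort selected on its future. If the two groups lose patients at different rates, the selection differs by group, and a difference can appear where there is none.

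**Working it through.** **1. What the criterion does, case by case** (endpoint = death)

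| Course of the patient | Criterion (3) as written |
|---|---|
| Dies under follow-up at any time | met |
| Followed alive beyond 2 years | met |
| Lost alive before 2 years | not met |

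**2. Against the planned loss.** At 80% follow-up, 120 × 0.20 = 24 patients per group are expected not to complete follow-up. Under the literal criterion, those lost alive were never eligible. The cohort would have complete follow-up by construction, and an allowance for loss would have no role within it.

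**3. The plan's own figure.** Inputs are 11 (SD 4) and 9 (SD 3) months, α = 0.05 and β = 0.10.

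n = (1.960 + 1.282)² × (4² + 3²) / 2² = 10.51 × 6.25 = 65.7, so 66 per group (two-sided). This matches the stated 66. The means and SDs used below are therefore the ones the plan relied on.

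**4. Size of the bias in one group.** Assume a constant loss rate λ, independent of prognosis, until the earlier of death and 24 months. A patient with survival time t is retained with probability exp(−λ·min(t, 24)). Longer survivors are retained less often, so the retained cohort is shifted towards early deaths.

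Worked case: exponential survival, mean 11 months, 20% lost.

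- P(lost) = λ/(λ + 1/11) × [1 − exp(−24(λ + 1/11))] = 0.20 gives λ ≈ 0.0246 per month, and λ + 1/11 ≈ 0.1155.
- Retained distribution up to 24 months: F(t) = 0.787 × [1 − exp(−0.1155t)] / 0.80, where 0.787 = 0.0909/0.1155.
- Median: 1 − exp(−0.1155t) = 0.40/0.787 = 0.508, so t ≈ 6.1 months. The true median is 11 × ln 2 = 7.6.
- 12-month OS: 1 − 0.787 × (1 − 0.250)/0.80 = 26.2%. The true value is exp(−12/11) = 33.6%.

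Simulation (1,000,000 patients per scenario) gives the same values, and the following:

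| Survival shape (assumed) | Loss | True median (months) | Retained median (months) |
|---|---|---|---|
| Gamma, 11 (SD 4) | 20% | 10.5 | 10.2 |
| Gamma, 9 (SD 3) | 20% | 8.7 | 8.5 |
| Exponential, mean 11 | 10% | 7.6 | 6.9 |
| Exponential, mean 11 | 20% | 7.6 | 6.1 |
| Exponential, mean 11 | 30% | 7.6 | 5.4 |
| Exponential, mean 9 | 20% | 6.2 | 5.0 |

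The gamma rows match the protocol's means and SDs. The exponential rows have SD equal to the mean, which is far wider than the protocol states. With gamma survival and a different loss model (40% of patients given a uniform 0-24 month loss time), 18% and 15% are lost and the medians are again 10.5 to 10.2 and 8.7 to 8.5.

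**5. Two groups with identical true survival, mean 10 months** (loss rates assumed)

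- Gamma, SD 3.5, about 10% versus 29% lost: retained medians about 9.5 and 9.2, a false difference of about 0.3 months.
- Exponential, 10% versus 30% lost: retained medians 6.3 and 4.9, a false difference of about 1.4 months.

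The planned difference in means is 11 − 9 = 2 months.

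**6. Direction**

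- If the chance of ever being lost is unrelated to survival time, the median stays at 7.6 months (exponential, mean 11), so there is no bias.
- If frail patients are lost at 8 times the rate of others, with 20% lost overall, the median still falls, from 6.0 to 5.1 months.
- A strong enough preference for losing patients close to death would raise the retained median instead.

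**The case against.** The best defence is that criterion (3) is a loosely worded requirement for prospective follow-up. The criteria are tied to enrolment and consent, and the design is called prospective. The Results section says enrolled patients are already being visited, so people are being entered before their 2-year status can be known. The 80% follow-up rate implies that enrolled patients are expected to be lost. The planned survival methods accommodate censoring, and the Strengths and Limitations section accepts online interviews to limit dropout.

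Most of this stands as evidence about intent. A reader might infer that patients lost alive are, or will be, dropped from the analysis. The article does not say so, and that cannot be asserted. The defence does not rescue the wording, however. Read as an intention to attend, criterion (3) adds little to voluntary participation and exclusion (4). Read literally, it filters on the outcome. No sentence settles which is meant.

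A reader might also see the same fault in exclusion (4). That clause is an ordinary screening exclusion, assessable at consent, and nothing suggests it would be applied retrospectively.

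Finally, a reader might infer a bias of 1 to 3 months. The upper end needs exponential survival with a 20-month mean that the protocol does not state, and almost no loss in one group. The protocol's own SDs give far less.

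**Conclusion.** The criterion is wrong as written: it cannot be judged at entry, and it makes eligibility depend on OS. Whether it would be used to remove patients is not stated, so the bias is conditional on literal application.

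Given literal application and loss that accrues over time independently of prognosis, OS is biased downward. The size depends mainly on the spread of survival times. It is small under the planning SDs and becomes material, relative to a 2-month planned difference, only if survival is much more dispersed than planned. A false group difference further requires unequal loss, and the protocol gives no group-specific rates. It would not be right to say that OS will certainly be underestimated, because the direction depends on who is lost. Selecting on future follow-up is unjustified whichever way the bias runs, and its size cannot be known in advance.

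**What to change.** Delete inclusion criterion (3), or reword it as willingness to attend the follow-up schedule, judged at consent. Add one sentence stating that every enrolled patient is analysed for OS, with those lost alive censored at the date last known alive. Exclusion (4) can stay, provided it is applied only at screening.

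Enrolment began in June 2022, so the sponsor should also confirm that no enrolled patient has been removed under criterion (3), and reinstate any who have been.

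The cost is a wording change and a check of the enrolment log. It needs no extra visits and no extra patients, and it should be settled before any OS analysis.

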**Figure 1 figure1:**
[figure not shown]
Study flowchart. ASIA: American Spinal Injury Association; CT: computed tomography; ECOG: Eastern Cooperative Oncology Group; ESCC: esophageal squamous cell carcinoma; KPS: Karnofsky Performance Scale; MRI: magnetic resonance imaging; PET-CT: positron emission tomography–computerized tomography; SMLC: spinal metastases of lung cancer; VAS: visual analogue scale.

### Treatment

A surgical decision is made following the advice of our institutional multidisciplinary treatment team for spinal metastasis. There are 3 indications for surgery at our center: severe yet drug-resistant local pain, progressive neurological dysfunction, and emerging or latent spinal instability. Otherwise, patients are referred for nonsurgical treatment.

In the surgical group, patients are given surgical treatment, neurological rehabilitation, and adjuvant therapies (ie, SBRT and antitumor drugs). In this setting, we have established a synchronized workflow for surgery-based multimodality therapy instead of the conventional step-by-step schedule. A synchronized workflow means that neurological rehabilitation is incorporated and commenced right before the surgery and that SBRT and antitumor drugs are started early and simultaneously during the process of rehabilitation.

In the nonsurgical treatment group, patients are treated with adjuvant therapies exclusively, including radiotherapy, chemotherapy, targeted therapy, immunological therapy, etc. Considering the existence of various adjuvant modalities, this study will only enroll patients who receive both locoregional radiotherapy and antitumor drugs.

